### Recruitment

Patients will be identified by searching general practitioners' lists for those with a diagnosis of IBS and by opportunistic recruitment of patients presenting with symptoms consistent with IBS. We will utilise the English Primary Care network (PCRN) to aid recruitment and retention of GP practices. We will include practices with urban and rural settings and with a range of socio-demographic characteristics. GP practices willing to participate in the study will search their list for patients aged 16 to 60 with a diagnosis of IBS. Potential participants will be contacted by letter (sent by the GP surgery) informing them about the trial and inviting them to take part. The GPs will check the lists of patients to be contacted prior to the invite letters being sent out to ensure that it is appropriate to contact them. The mailing will include the MIBS patient information sheet. Participants who are interested in participating in the study will return a reply slip with their contact details in a prepaid response envelope to the research team. The reply slip will also enclose a decline sheet where the participants can tick the option that describes the reasons why they have decided to decline the invitation. GPs will also be able to opportunistically provide information about the trial to potential recruits during their GP surgeries. If a patient with IBS attends a GP consultation, GPs will give them the patient information sheet regarding the trial and the reply slip and envelope.

### Intervention

135 patients will be randomised to: mebeverine (135 mg three times a day), methylcellulose (3 tablets twice a day), or a placebo tablet for 6 weeks. To ensure double blinding, all participants will take three over-encapsulated identical tablets in the morning, one at lunchtime and three at teatime.

They will also be randomised to 1 of 3 website conditions: access to Regul8 with a 30-45 minute nurse telephone session after session 2 (to encourage engagement with the CBT programme) and email support on request, the website with minimal support (i.e. technical email support on request), or no website, thus creating 9 groups.

There will be double-blinding for medication groups, single-blinding for the website (participants will not be able to be blind to website access). Website access will be with a personal password so that usage can be assessed. All patients will receive a telephone call in the first week to check they have no problems with the medication or paperwork. Those not randomised to website access will receive standard patient information and will be offered access to the website at the end of the trial.

### Telephone session

The telephone session in the first website condition will be scheduled after patients complete session 2 where they develop their own personal model on the website of how their thoughts, feelings and behaviours might be contributing to their IBS symptoms. The purpose of the session is for the patients to clarify their model with the nurse, for the nurse to help patients extend their model where they may have left out relevant material, and to motivate patients to continue using the website by linking the sessions back to the information they provide. Patients will also be given the opportunity to discuss any technical difficulties they may have and encouraged to email the nurse if they wish to clarify any information on the site or have any difficulties in the future.

Prior to the start of the trial the nurse received 4 hours training in the telephone protocol which included outlining the protocol, training in the basic principles of CBT and listening skills, practice role play sessions which were audiotaped and discussed in supervision sessions with [name]. All sessions will be audiotaped and saved in password protected anonymous files. Throughout the trial, audiotapes will be sent to [name] and the nurse will receive regular supervision (after each session for the first 4 sessions and 4 random sessions thereafter. This will ensure the quality the intervention as well as allow us to assess fidelity regarding the protocol. The timing and length of each telephone session will be recorded, as well as the number of email contacts per participant both in the telephone and email only conditions.

### Trial medication

Will be over-encapsulated active mebeverine 135 mg tablets, over-encapsulated active methylcellulose 500 mg tablets and over-encapsulated placebo (candarel) tablets all to be taken orally. All patients will receive medications of the same shape and colour. The patients will be supplied with 6 weeks of medication by the research nurse. To ensure double blinding, all participants will take 3 over-encapsulated identical tablets in the morning, one at lunchtime and three at teatime.

The medications will be supplied by SCM Pharma and fully QP released in line with MHRA regulations and cGMP procedures. SCM pharma will produce all patient kits according to the randomisation list and will supply code break envelopes to ensure patient safety.

The medications are being supplied in two packing campaigns, with a shelf life of 12 months. The study medications will be stored and dispensed by the trials site pharmacy in accordance with Good Clinical Practice and Good Manufacturing Guidelines. All the participants will receive a Medication Diary Sheet where they will keep a daily record of the numbers of tablets taken during the six week period.

### Data collection

Participant data will be collected on the MIBS trial website. Baseline data will be collected from included patients before randomisation and will be co-ordinated by the trial manager who will be blind to treatment allocation. All baseline and outcome data is patient self-completed away from the study team, thus avoiding any influence of the study team on the responses and reducing bias. Participants will be given a unique password to log onto the website. Their data will be identified by a unique identification number and will be kept separate from any personal identifying data to maintain confidentiality.

An on-line baseline assessment which includes socio-demographic details and the measures detailed below will be completed by all participants prior to the nurse visit and before randomisation. These are well-recognised, validated measures that are widely used and will enable us to gain a clear picture of participants IBS and the impact it has on their lives.

Those randomised to the self management programme will complete on-line symptom severity questions, symptom, food and exercise diaries, questions about stress and triggers and their symptoms and their coping strategies. These data will be collected and stored and may be used to provide information to assess the self management programme but will mostly be used by the participants themselves to monitor their progress and inform themselves about their own symptoms, triggers and coping strategies as part of the cognitive behavioural therapy based self-management programme.

Outcome data and questionnaires outlined below will be completed at 6 and 12 weeks post randomisation by all participants. Participants will be sent a reminder email at 6 and 12 weeks to prompt them to complete the questionnaires. If it has not been completed within one week of the reminder, a further reminder will be sent. One week after that, if no data has been entered, the research nurse will ring the participant to ask if she can collect the data over the telephone.

The patients GP notes will be reviewed at 12 weeks to assess the number of GP contacts in the year prior to entering the study and in the 3 months since the study. In a full trial a one year notes review is planned. Other studies have shown an impact on GP contacts from patient self management programmes[22].

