The research nurse will telephone all participants in the trial in the first week after randomisation (see randomisation procedure above) to check they have no problems with the medication or paperwork and to ensure they can log onto the MIBS website. The nurse will also make a time for a phone call session with those randomised to the Regul8 self-management programme with nurse support (see section above for details on telephone session protocol and timing). They will also be able to email the nurse regarding queries about the website programme during the study. Medical questions will not be addressed by the research nurse and participants will be advised to seek medical advice if they have medical queries. Those randomised to website alone will be offered technical website support by email.

Those not randomised to receive the website programme will receive normal GP care. All the randomised participants will receive normal GP care during the trial if they require it.

The trial medication for the MIBS Study is over-encapsulated to maintain blinding but is quite large and preliminary work indicated that some participants may find it difficult to swallow. If participants were considering withdrawal from the trial due to the size of the medication and swallowing problems, they will be permitted to open the medication capsules to enable them to continue to take the medication and stay within the trial. The Research Nurse (RN) will discuss medication taking with any participants who indicate that they are finding it difficult to take. If they indicate that they cannot manage to take the trial medication because of swallowing problems with the capsules, the RN will provide the option that they could open the capsules by twisting them and taking the medication inside the capsule. This is smaller than the entire capsule and thus would mean the medication is easier to swallow and should enable retention of these participants within the study.

These participants will potentially be un-blinded as they will see the tablets. However, participants will be recording their medication taking in diaries and will be asked to guess which medication they are on - enabling assessment as to whether opening the capsule un-blinds the participants. We will record which participants open the capsules. Intention to treat analysis will be maintained but will include the opening of the capsules as factor within the analysis of the data.

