### Primary Outcome measures

Change in the Irritable Bowel Symptom Severity Scale (IBS SSS score) and IBS Quality of Life Questionnaire (IBS-QOL) from baseline to 12 weeks.

The IBS SSS [23] is a 5 item self-administered questionnaire measuring: severity of abdominal pain, duration of abdominal pain, abdominal distension/tightness, bowel habit, quality of life. Maximum score 500: < 75 normal bowel function, 75-174 mild IBS, 175-299 moderate IBS, 300-500 severe IBS). The IBS-QOL[24] is an extensively validated quality of life measure for IBS: 34 items, 8 subscales, item responses graded on a 5 point scale, total score 0-100 with higher scores indicating better health related QOL. Administered at baseline and 6 weeks (end of treatment) and12 weeks (6 months and 12 months would also be planned for the full trial).

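### Late primary outcomes are to be taken by telephone by the research nurse, who on the natural reading also delivers the telephone support, although the article says patients complete every outcome without the team

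*Protocol article*

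**What the plan says.** Four parts of the protocol article bear on this.

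- **Data collection** gives the safeguard: "All baseline and outcome data is patient self-completed away from the study team, thus avoiding any influence of the study team on the responses". It sets the time points: "Outcome data and questionnaires outlined below will be completed at 6 and 12 weeks post randomisation by all participants". It then describes an email reminder, a second reminder a week later and, a week after that, the fallback: "the research nurse will ring the participant to ask if she can collect the data over the telephone". The only role described here as blind is the trial manager. Baseline data are "co-ordinated by the trial manager who will be blind to treatment allocation".
- **Primary Outcome measures** names what is at stake: "Change in the Irritable Bowel Symptom Severity Scale (IBS SSS score) and IBS Quality of Life Questionnaire (IBS-QOL) from baseline to 12 weeks".
- **Study Procedures** has the research nurse telephone every participant in the first week and continues: "The nurse will also make a time for a phone call session with those randomised to the Regul8 self-management programme with nurse support". Participants in that arm may also email the nurse with queries about the programme. **Telephone session** describes what happens in the call: "The purpose of the session is for the patients to clarify their model with the nurse". It also gives her the task of motivating further use of the site.
- **Intervention** describes the website factor as "single-blinding for the website (participants will not be able to be blind to website access". **Randomisation** says that the research nurse does not know the medication. It makes no such statement for the website condition.

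**The concern.** The article names influence of the study team on responses as the bias to be avoided, and offers self-completion as the protection. The telephone fallback removes that protection for late responders, and the caller is not a neutral member of the team. IBS SSS and IBS-QOL are self-reported and subjective. Some patients would give their scores to the person who had worked through their personal model with them and encouraged them to keep using the site. Others would give them to someone who had not.

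A reporting difference of that kind would not be shared equally by the arms. It bears mainly on telephone support versus minimal support, and the second question listed under Aims uses the pilot to choose between these two for the full trial. Since the pilot is also meant to test all the trial procedures, an uncorrected procedure would carry over into the definitive trial.

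**Working it through.** No figure in the article depends on this point, so the check is mainly a comparison of sections.

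**1. Is there a contradiction?** Data collection says that all outcome data are self-completed without the team. The same section has a team member take late outcome data by telephone. Both statements cover 6 and 12 weeks. They cannot both hold for a participant who has not answered two reminders.

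**2. Is the caller the person who delivers the support?** No sentence says outright that the research nurse delivers the telephone session. Study Procedures begins with the research nurse making the week-1 calls, then says that the nurse books the session and can be emailed. Telephone session refers throughout to one nurse, trained before the trial started. No second nurse and no separate outcome caller is described. One nurse in all these roles is the natural reading.

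**3. What does she know?**

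| Allocation | Basis in the article | Status |
|---|---|---|
| Medication | Randomisation: nurse is unaware of it | Blind |
| Telephone arm versus the other two | Study Procedures: nurse books the session | Not blind |
| Minimal support versus no website | Study Procedures: the pack given at the nurse appointment holds either website details or written information; whether she sees which is not said | Likely known, not stated |

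**4. How large could it be?** The documents give neither the share of outcomes taken by telephone nor any reporting shift, so what follows is an assumption-based illustration. Let *p* be the share of an arm collected by telephone. Let *s* be a shift common to everyone who speaks to the nurse, and *d* the extra shift among patients she has supported. The bias in the telephone-minus-minimal contrast is

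*p*(tel) × (*s* + *d*) − *p*(min) × *s* = *s* × [*p*(tel) − *p*(min)] + *p*(tel) × *d*.

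With equal shares the common part cancels and *p* × *d* remains. Each website level has 135/3 = 45 patients. After the planned 20% drop-out, 45 × 0.8 = 36 remain. With the article's SD of 80 and no gain from baseline adjustment, SE = 80 × √(2/36) = 18.9. The type I error of a two-sided 5% test with bias *b* is 1 − Φ(1.96 − *b*/SE) + Φ(−1.96 − *b*/SE).

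| Assumed *p* | Assumed *d* (points) | Bias (points) | Share of the 53-point target | Type I error |
|---|---|---|---|---|
| 10% | 10 | 0.10 × 10 = 1 | 1/53 = 2% | 5.0% |
| 20% | 20 | 0.20 × 20 = 4 | 4/53 = 8% | 5.5% |
| 30% | 40 | 0.30 × 40 = 12 | 12/53 = 23% | 9.8% |

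Shares of 10% to 30% correspond to about 4 to 11 of the 36 patients (0.10 × 36 = 3.6; 0.30 × 36 = 10.8). If ANCOVA reduces the SE, the same bias counts for somewhat more.

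**The case against.** The best case for the plan is that the alternative to the call is usually a missing primary outcome, not an online one. The article already allows for 20% drop-out, and missing data may themselves differ by arm. The fallback starts only after two reminders. The nurse meets and telephones participants in every arm, so part of any wish to please her is common to all arms. Her treatment role is a single session of 30 to 45 minutes plus email contact. This is also a pilot whose main products are feasibility findings.

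Much of this stands. It is a good reason to keep the telephone fallback and to expect a modest effect. It does not justify giving the call to the person who provides the support, and it does not reconcile the two statements in Data collection.

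A reader might go further in three ways that the documents do not support.

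- One might infer that the nurse knows every website allocation, so that website versus no website is equally compromised. Only her knowledge of the telephone arm follows from the text.
- One might assert that supported patients will answer favourably, and by a given amount. The article contains nothing on either the direction or the size.
- One might ask for the website factor to be relabelled open-label. Intervention already says plainly that participants are not blind to website access, so a new label would change no procedure.

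**Conclusion.** The point holds in limited form. The statement that all outcomes are self-completed is contradicted within its own section. The fallback lets a person who is not blind to the telephone arm, and who on the natural reading delivers its support, collect subjective primary outcomes. This permits differential reporting among late responders, chiefly in the comparison of telephone with minimal support.

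The size is unknown. The 1 to 12 points above reflect assumed inputs only and are not an estimate. The drug factor is not affected, because the nurse does not know the medication.

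The conclusion rests on one inference, that the research nurse and the nurse who runs the sessions are the same person. If they are different people, the contradiction remains, but the concern about the caller's role and knowledge weakens. The change should be made because it is cheap and protects a comparison that informs the design of the full trial. It does not call the trial as a whole into question.

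**What to change.** 1. Keep the telephone fallback. Have the calls made from a fixed script by an existing team member who provides no website support and is not told the website allocation, for example the trial manager. Ask participants at the start of the call not to disclose their website condition.
2. Record for each outcome and visit whether it was completed online or by telephone, and run a sensitivity analysis restricted to online responses.
3. Reword the sentence in Data collection to say that outcomes are self-completed online, with telephone collection by a named role for participants who do not respond to reminders.

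The cost is a little extra work for the person who takes over the calls. There is also a small risk that participants reveal their allocation and so unblind the caller. This matters somewhat if the caller is the trial manager, the only role that Data collection describes as blind. Another uninvolved team member would avoid that.

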### Study Procedures: (See Additional File 1)

Those responding to the recruitment letter from their GP will be asked to complete a screening on-line questionnaire consisting of the Rome III criteria and questions about exclusion and inclusion criteria to check if they fulfil the eligibility criteria for the study. They will log on to the MIBS trial website with a unique ID number. Any patient indicating they may have a 'red flag' symptom that would indicate the need for further investigations (i.e. unexplained weight loss or rectal bleeding) will be referred back to their GP and would not enter the study.

Those who are eligible to enter the trial will be telephoned by the research nurse and offered a meeting with the research nurse at their GP practice to discuss the trial and complete consent forms. At this meeting a blood sample will be taken from the participant by the research nurse for a full blood count (FBC), transglutaminase antibodies (TTG) and a C-Reactive protein (CRP) to exclude alternative diagnoses i.e. anaemia that requires further investigation and Coeliac disease. The results will be made available to the participants GP. The blood sample will not be stored for future use.

Once the blood test result is known and the patients eligibility for the trial is confirmed (i.e. no abnormalities on the blood test) a further nurse appointment will be made and the participant will be given a recruitment pack containing their trial medication and an information sheet about the website and website password, or written patient information on IBS. If the blood tests show an abnormal result i.e. an CRP over the normal laboratory range or anaemia or a positive test for Coeliac disease the patient will not be randomised to the trial but will be referred back the their GP for further assessment.

The research nurse will telephone all participants in the trial in the first week after randomisation (see randomisation procedure above) to check they have no problems with the medication or paperwork and to ensure they can log onto the MIBS website. The nurse will also make a time for a phone call session with those randomised to the Regul8 self-management programme with nurse support (see section above for details on telephone session protocol and timing). They will also be able to email the nurse regarding queries about the website programme during the study. Medical questions will not be addressed by the research nurse and participants will be advised to seek medical advice if they have medical queries. Those randomised to website alone will be offered technical website support by email.

Those not randomised to receive the website programme will receive normal GP care. All the randomised participants will receive normal GP care during the trial if they require it.

The trial medication for the MIBS Study is over-encapsulated to maintain blinding but is quite large and preliminary work indicated that some participants may find it difficult to swallow. If participants were considering withdrawal from the trial due to the size of the medication and swallowing problems, they will be permitted to open the medication capsules to enable them to continue to take the medication and stay within the trial. The Research Nurse (RN) will discuss medication taking with any participants who indicate that they are finding it difficult to take. If they indicate that they cannot manage to take the trial medication because of swallowing problems with the capsules, the RN will provide the option that they could open the capsules by twisting them and taking the medication inside the capsule. This is smaller than the entire capsule and thus would mean the medication is easier to swallow and should enable retention of these participants within the study.

These participants will potentially be un-blinded as they will see the tablets. However, participants will be recording their medication taking in diaries and will be asked to guess which medication they are on - enabling assessment as to whether opening the capsule un-blinds the participants. We will record which participants open the capsules. Intention to treat analysis will be maintained but will include the opening of the capsules as factor within the analysis of the data.

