### Analysis

An intention-to-treat analysis, of change in the IBS SSS and IBS-QOL at baseline, 6 weeks and 12 weeks (6 mnth and 1 yr are planned for the full trial) will be undertaken by ANCOVA for a factorial trial. In the main trial (but not in the pilot): subgroup analysis will be performed using regression modelling to determine if symptoms subgroup (diarrhoea-predominate, constipation-predominate and alternating symptoms) predicts differences in outcome. Other potential factors that may affect outcome will be explored: severity of presenting symptoms, duration of presenting symptoms, age and sex.

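### Capsule opening, a self-selected behaviour after randomisation, is named as a factor in the intention-to-treat analysis; the primary ANCOVA should leave it out

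*Protocol article*

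**What the plan says.** The protocol article deals with capsule opening under Study Procedures. It first sets out who may do it: "If participants were considering withdrawal from the trial due to the size of the medication and swallowing problems, they will be permitted to open" the capsules. It accepts a consequence for blinding ("These participants will potentially be un-blinded as they will see the tablets") and plans to capture the behaviour ("We will record which participants open the capsules"). Participants are also asked to guess their medication, so that any unblinding can be assessed. The analysis rule follows: "Intention to treat analysis will be maintained but will include the opening of the capsules as factor within the analysis of the data".

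The Analysis section says that the intention-to-treat analysis of IBS SSS and IBS-QOL "will be undertaken by ANCOVA for a factorial trial". It does not mention capsule opening. Neither section says whether the model with opening is the primary one or a secondary one.

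Two other statements bear on whether opening could differ between arms. Under Intervention, "all participants will take three over-encapsulated identical tablets in the morning, one at lunchtime and three at teatime", whatever the drug. One website arm gets "access to Regul8 with a 30-45 minute nurse telephone session after session 2", while the call that checks for medication problems goes to everyone: "The research nurse will telephone all participants in the trial in the first week after randomisation".

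**The concern.** Adjusting for a baseline covariate preserves a randomised comparison. Adjusting for something that happens after randomisation need not. Once opening is in the model, the treatment coefficient is a weighted average of openers against openers and non-openers against non-openers. Randomisation does not make those subsets comparable. Participants close to withdrawing may differ from the rest in severity or motivation, and the decision to persist by opening the capsules, rather than stop, could depend on how well the assigned treatment seems to be working.

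Two things follow if opening depends on arm. If opening is also related to outcome for other reasons, the adjusted effect is biased while the unadjusted one is not. If opening is itself partly an effect of treatment and affects outcome, part of the treatment effect is adjusted away. Either way the result is not the intention-to-treat effect that the sentence says is kept.

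The factor also does not deal with the problem that prompted it. Unblinding would be expected to push placebo openers and active-drug openers in opposite directions, and a single main effect for opening cannot absorb that.

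The comparisons at stake are those on both primary outcomes. The Aims and Discussion say that the pilot's results and estimated effects will inform the full trial, so the rule could also be carried forward.

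**Working it through.** **Reference scale.** The Sample size section gives a difference of 53 points, SD 80, 80% power and 95% confidence (read as two-sided 5%), with 35 per group. Check: n = 2(1.960 + 0.842)² × 80² / 53² = 35.8, so 36 per group, one more than stated. Power at 35 is 79.1%. With 135 recruited and 20% lost, 135 × 0.8 / 3 = 36 per drug level or website level. The standard error of an unadjusted difference is then 80 × √(2/36) = 18.9 points.

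**Formula for the shift.** For least squares without other covariates, this identity is exact:

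adjusted effect = unadjusted effect − b × (p1 − p0)

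Here p0 and p1 are the proportions opening in the two arms, and b is the coefficient for opening in the adjusted model. If p1 = p0 or b = 0, the shift is zero.

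**Model for b (assumptions; the protocol gives no opening rates).** Each participant has a standard normal trait U. A participant opens the capsules when U exceeds the arm's cut-off, and U worsens the score by g points per SD, with total SD 80. With equal arms:

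b = g × [φ(z0) + φ(z1)] / [p0(1 − p0) + p1(1 − p1)]

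where z is the normal cut-off for each p, and φ = 0.1755, 0.2332, 0.2800 and 0.3477 at p = 0.10, 0.15, 0.20 and 0.30.

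Worked case, 10% v 30%, g = 25: b = 25 × 0.5232 / 0.30 = 43.6; shift = −43.6 × 0.20 = −8.7.

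| Opening, arm 0 v arm 1 | g | b | Shift | Adjusted estimate if the true effect is −53 |
|---|---|---|---|---|
| 10% v 10% | 25 | 48.7 | 0 | −53.0 |
| 10% v 15% | 25 | 47.0 | −2.4 | −55.4 |
| 10% v 20% | 25 | 45.5 | −4.6 | −57.6 |
| 10% v 30% | 25 | 43.6 | −8.7 | −61.7 |
| 10% v 30% | 40 | 69.8 | −14.0 | −67.0 |

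Simulation agrees: unadjusted about −53 throughout; adjusted about −57.6, −61.7 and −66.8 in the 10% v 20% row and the two 10% v 30% rows. A 5% v 30% split with g = 40 would give about −17.5, but it is a more extreme imbalance than anything the protocol suggests. The sign depends on which arm opens more: here the active arm does, and the benefit is exaggerated; reversed, it would be diluted.

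**With a baseline covariate.** ANCOVA normally adjusts for baseline score. Suppose that score correlates r with U, and add it to the model. At 10% v 30%:

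| g | r = 0 | r = 0.5 | r = 0.8 |
|---|---|---|---|
| 25 | −8.7 | −7.4 | −4.4 |
| 40 | −14.0 | −11.8 | −7.1 |

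**Unblinding.** Take a true effect of 0, 20% opening in each arm, placebo openers 30 points worse and active openers 30 points better. The unadjusted difference is 0.20 × (−30) − 0.20 × 30 = −12. Opening is balanced, so the identity gives an adjusted difference of −12 as well. The factor removes none of the distortion.

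**The case against.** The best defence is that the condition for bias is unlikely to be met to any great extent. All drug arms take capsules of the same appearance, number and schedule, and opening is allowed because of capsule size and swallowing difficulty, neither of which depends on the contents. Poor tolerability of the drug is not a stated reason for opening. This stands as an argument against large imbalances between drug arms. It does not rule out smaller ones, because persisting instead of withdrawing can depend on perceived benefit.

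A reader might infer that the website comparison is equally exposed, since the nurse who offers opening also spends more time with one website arm. The documents do not support going that far. The first-week medication call goes to all participants, the longer session concerns the personal model, engagement and technical difficulties, and the nurse does not answer medical questions. The route is possible but not shown.

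It can also be said that the Analysis section leaves the factor out, so that the Study Procedures sentence may mean only an additional look. That reading needs words the sentence lacks: it attaches the factor to the intention-to-treat analysis and does not call it a sensitivity analysis. An unseen analysis plan may settle the matter, but the protocol as it stands gives two descriptions of one analysis.

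Finally, this is a feasibility pilot that disclaims power for a definitive effect, and a shift of 4 to 5 points is about a quarter of the 18.9-point standard error. That lowers the urgency. It does not make the rule sound.

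**Conclusion.** The concern holds in conditional form. The protocol states a rule under which the intention-to-treat model contains a self-selected behaviour that follows randomisation, and its Analysis section describes the model without it. The adjusted comparison is biased if opening differs by arm and is related to outcome; with balanced opening it is not.

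Under the assumed rates and trait strengths the shift is 0 to about 14 IBS SSS points, or up to 14/53 = 26% of the target difference. It is about 2 points at 10% v 15% with g = 25, and about 4 to 7 points even at 10% v 30% if the baseline score captures most of the trait. These rates and strengths are assumptions, not figures from the protocol.

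A reader might infer that the trial's drug and website effects will be materially biased, with 9 to 14 points as the expected size. The documents do not support that: those values need a threefold difference in opening, which identical capsules make unlikely, and no baseline adjustment. This should be fixed before analysis, but it does not defeat the pilot's purpose. Recording opening and the treatment guess is sound as planned.

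**What to change.** Replace the analysis sentence in Study Procedures, and align the Analysis section with it, along these lines: the primary intention-to-treat factorial ANCOVA includes only the randomised drug and website factors and baseline covariates; capsule opening is not in that model. The number opening capsules is reported by drug arm and by website arm, with the treatment-guess data shown by opening status. Any analysis that uses opening is a sensitivity or exploratory analysis and is labelled as a non-randomised comparison.

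The cost is a change of wording. Opening and treatment guesses are already to be collected, and the sample size does not change. The fix concerns the analysis only and leaves the arrangement for opening capsules as it is.
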